### Ethics and dissemination

This study protocol was approved by the UVRI Research Ethics Committee (REC) (number:
G.C./127/21/09/858), the LSHTM REC (number: 26638) and the Uganda National Council for
Science and Technology (protocol number: HS1791ES). Written informed consent will be
obtained from all participants before conducting study procedures. Participants must
provide consent for all study procedures to be eligible to participate in the study,
including consenting for biospecimens to be stored for future research purposes. Consent
to publication will be obtained as part of consent to participation in the study. Research
findings will be disseminated in policy briefs, seminars, local and international
conferences and publications in peer-reviewed open-access journals. As part of the
dissemination plans, findings will also be disseminated to patient care groups and to
clinicians in the participating hospitals.

## Discussion

This study aims to determine the prevalence of diabetes and pre-diabetes and establish a
cohort of patients with diabetes to understand the course of these different phenotypes,
including how people living with diabetes respond to treatment. We expect these data to be
of direct relevance to an improved understanding of the pathophysiological basis of
diabetes, the performance of diagnostic tests and management of diabetes in SSA, and
ultimately to lead to better outcomes and well-being of patients and increased productivity.
This protocol has been developed based on standard guidelines for diagnosing and managing
individuals with diabetes and sought input from experts in this disease area.

Based on the considerable sample size to be enrolled in this study, we expect to generate a
large population-based dataset that will provide a reliable estimate of the burden of the
disease within this population. To minimise bias within our study, (1) all the research team
members have been well trained on the research study protocol, (2) research assistants have
been trained on the administration of the questionnaires, (3) checks have been implemented
within the electronic case report form to minimise on the missingness of data related to
questionnaire administration, and (4) measures have been put in place to minimise loss to
follow-up during the follow-up phase of the study. In addition, unresponsiveness was
accounted for during the sample size calculation.

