this condition appears to occur in relatively young and lean individuals in Africa and other
LMICs. This evidence initially came from Southeast Asia, where people were observed to
develop type 2 diabetes at lower levels of obesity than white Caucasians; this has led to
Asia-specific lower body mass index (BMI) thresholds for defining obesity.^9^ The explanation has been that Southeast Asians have a
propensity towards central obesity (and therefore insulin resistance) at relatively low body
weight. Our group recently showed that 50% and nearly 40% of newly diagnosed
type 2 diabetes (negative for pancreatic autoantibodies) in Uganda are younger than 50 years
and have a BMI of ≤25 kg/m^2^, respectively.^10^ In contrast to observations in Southeast Asia, the
‘thin’ patients showed no evidence of excess ectopic or visceral fat (using
anthropometric and electric bioimpedance measurements) or insulin resistance. Instead, they
had features consistent with insulin deficiency (lower fasting insulin, C peptide
insulinogenic index and Homeostatic Model Assessment for Insulin Resistance (HOMA-IR)).^11^

These observations raise important research questions and have huge potential clinical
implications: what are the mechanisms that drive diabetes in Africa; what are the right
approaches to its prevention and management? For example, are the lifestyle
interventions targeting weight loss or metformin use (as an insulin sensitiser), two
traditionally recommended first-line management options for type 2 diabetes, effective in
Africa?

This necessitates rigorous studies to unravel the complex manifestations of diabetes in
Africa and identify the right approaches to prevention and management. Therefore, in the
Diabetes in low-resource Populations Study, we aim to: (1) determine the prevalence of
diabetes in Uganda, (2) identify and characterise the different diabetes phenotypes, and (3)
develop a cohort in which we can examine and understand the course or progression of this
disorder and its different diabetes phenotypes. All patients except those with a known
diagnosis of diabetes (on oral or insulin treatment for diabetes) will undergo OGTT. With
this approach, we will be able to compare the diagnostic accuracy of fasting glucose and
HbA1c with OGTT.

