### Study setting

The study will be conducted in Uganda. Uganda is undergoing urbanisation, but more than
70% of the population still lives in rural areas. The study shall recruit from two
sites (rural and periurban areas) across the greater Masaka region in southwest Uganda to
explore the differences in lifestyle and how these influence the prevalence of diabetes
and its outcomes. The GPC in Kyamulibwa subcounty, Kalungu district in southwest Uganda,
will provide the rural population and the town of Lukaya, the periurban population. Both
rural and periurban sites are established research areas.

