### Sample size determination

This study is powered to estimate the prevalence of diabetes and pre-diabetes with a high
degree of precision. We base our assumptions on results from the 2014 Ugandan nationwide
cross-sectional survey suggesting that the prevalence of impaired fasting glucose and
diabetes in Uganda is 2% (95% CI: 1.5% to 2.5%) and
1.4% (95% CI: 0.9% to 1.9%), respectively.^16^

Applying a rule of thumb that the margin of error should not exceed 0.25 of the
prevalence, and based on the following assumptions: (1) a margin of error of 0.5%
(a margin of error of 0.5–1% would be acceptable for low prevalence
conditions), (2) diabetes prevalence of 5% (assuming OGTT would detect twice more
cases of diabetes thus doubling the prevalence) and an estimated 5% level of
significance (z-value=1.96).

The minimum sample size is 7300 for a precision of ±0.5% and a
significance level of 5%. Assuming a response rate of 80% and further
adjusting for a design effect at 1.2, the required sample size of
(7300/0.8)×1.2=10 950. Therefore, we will aim to randomly screen a minimum
of 10 950 adults across all study sites.

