### Statistical considerations

Statistical analysis will be performed using STATA V.17 (StataCorp, Texas, USA). All
variables will be tabulated to assess distributions and to check for missingness and data
sparsity. Using descriptive statistics, categorical variables will be summarised as
frequencies and percentages. Continuous variables will be summarised as means and SDs or
medians and IQRs. Descriptive analysis will include key sociodemographic outcome
variables, for example, education level, socioeconomic status, baseline clinical
characteristics (age, sex, weight, BMI and waist circumference) and glycaemic control
characteristics (fasting glucose, 2-hour OGTT, HbA1c, fasting C peptide level).

Prevalence of diabetes will be computed as the number of diabetic cases at the end of the
study period as a proportion of the total number of participants enrolled into the study.
Similarly, prevalence estimates will be used to measure the burden of the different
vascular complications within this cohort. We will use Poisson regression analysis to
estimate the incidence rate of diabetes-related complications, including retinopathy,
nephropathy and neuropathy among individuals with diabetes and pre-diabetes. The
reproducibility of the diagnostic tests will be assessed by applying appropriate
diagnostic reproducibility statistics, including estimation of the dispersion of the data
values on index and repeat testing, interclass correlation and paired t-test (two tailed).
Furthermore, we will assess for percentage agreement using Bland-Altman’s methods
between the different tests. Before carrying out the analysis, test assumptions will be
checked. A two-sided p value of <0.05 will be considered a statistically
significant level for all analyses.

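### Primary prevalence is defined as a crude proportion of those enrolled, pooled over a rural and a periurban site, and the sample-size allowance for non-response is offered as protection against bias, which it cannot give

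*Protocol article*

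**What the plan says.** Under Statistical considerations, the article gives the estimator of the primary outcome: the count of people found to have diabetes by the close of the study, expressed "as a proportion of the total number of participants enrolled into the study". That section mentions no site-specific estimate, weight, standardisation or adjustment for non-response.

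Under Study setting, participants come from two sites, the rural general population cohort (GPC) in Kyamulibwa and the periurban town of Lukaya. They were chosen so that the effect of lifestyle differences on prevalence can be explored. Sample population counts 8864 adults in the first and about 10 000 in the second, all to be invited.

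Sample size determination starts from 7300 and then inflates: "Assuming a response rate of 80% and further adjusting for a design effect at 1.2", reaching 10 950. The Discussion names four measures to minimise bias: protocol training, questionnaire training, data-entry checks and steps against loss to follow-up. It then continues: "In addition, unresponsiveness was accounted for during the sample size calculation".

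The target population is described in more than one way. The Abstract (Methods) speaks of a rural Ugandan population. The Introduction aims to "determine the prevalence of diabetes in Uganda". The Primary study objective refers to a population-based cohort.

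**The concern.** Two statements in the text cause the difficulty; this is not a complaint about missing detail.

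First, a fraction whose denominator is the people enrolled depends on who came and from which site. If attendance differs by age, sex or site, and prevalence differs along the same lines, the headline figure shifts for reasons unrelated to disease burden. The protocol expects that the sites may differ, yet the only estimator it defines mixes them in whatever proportion attends.

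Second, the Discussion treats an inflated sample as help against bias. Dividing by the expected response rate ensures that enough people are measured. It does not make those measured resemble those who stayed away. None of the four numbered measures addresses survey non-response either, so a reader may believe that this source of bias has been dealt with.

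At stake is the meaning of the primary result. The study plans a margin of ±0.5 points, and a selection effect of the same order would not show in the confidence interval.

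**Working it through.** **Inputs from the documents.** Prevalence 5%, margin ±0.5 points, z = 1.96, response 80%, design effect 1.2 (all Sample size determination); 8864 rural and about 10 000 periurban adults (Sample population).

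**Inputs assumed here.** Prevalence in non-responders and prevalence by site. The documents give neither.

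**1. The plan's own figure.** n = z² p(1 − p)/d² = 1.96² × 0.05 × 0.95 / 0.005² ≈ 7299, stated as 7300. Then 7300/0.8 × 1.2 = 10 950, as stated. The arithmetic is sound.

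**2. What the inflation achieves.** With 10 950 approached and 80% responding, n = 8760. The half-width is 1.96 × √(1.2 × 0.0475/8760) = 0.500 points. The planned precision is met, and that is all the inflation does.

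**3. Bias from non-response.** Bias = (1 − response rate) × (prevalence in responders − prevalence in non-responders). Sample size does not appear in this formula. At 80% response with 5% in responders:

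| Assumed non-responder prevalence | Difference (points) | Bias (points) | Prevalence in all invited |
|---|---|---|---|
| 3.5% | 1.5 | 0.2 × 1.5 = 0.3 | 0.8 × 5 + 0.2 × 3.5 = 4.7% |
| 2.5% | 2.5 | 0.2 × 2.5 = 0.5 | 0.8 × 5 + 0.2 × 2.5 = 4.5% |

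The sign reverses if non-responders have the higher prevalence. A difference of 0.5/0.2 = 2.5 points is needed to use up the whole margin.

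**4. Dependence on site mix.** The rural share of the frame is 8864/18 864 = 47%. Assume 4% rural and 6% periurban. At the frame mix the pooled value is 0.47 × 4 + 0.53 × 6 = 5.06%. If 60% of those enrolled were rural, it would be 0.6 × 4 + 0.4 × 6 = 4.8%. Unequal take-up alone would move the crude figure by about 0.26 points, with both site prevalences unchanged.

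**5. Can site-specific estimates be afforded?** Splitting 8760 in the ratio 47:53 and dividing by 1.2 gives effective sizes of about 3430 and 3870. The margins at 5% are 1.96 × √(0.0475/3430) = 0.73 points (rural) and 1.96 × √(0.0475/3870) = 0.69 points (periurban). The plan calls 0.5 to 1% acceptable for low-prevalence conditions. These margins do not include any further loss from weighting.

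**The case against.** The strongest reply is that this is a condensed article. Every adult in both areas is invited, so a crude proportion weights itself unless response or take-up is uneven. The estimator sentence neither mentions sites nor excludes weights, comparison of the sites is an intended purpose, and weighting is commonly left to an analysis plan. The sentence on unresponsiveness also stands outside the numbered list. Much of this is fair. It limits the point to what is written: a formula with enrolled participants as denominator, and a sentence that places a precision device among the bias measures. Those two statements remain.

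Four stronger readings are tempting, and the documents do not support them.

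- **That the confidence intervals ignore the design effect.** No interval method for prevalence is stated, so this would be inferred from silence. Nor would simple binomial intervals necessarily be too narrow. If the target is the two study areas, the finite-population factor for 8760 of 18 864 is √(1 − 8760/18 864) = 0.73. The design-effect half-width then becomes 0.500 × 0.73 = 0.37 points, below the simple binomial 0.456.
- **That non-response is met only by enlarging the sample.** Mobilisers visit every household (Sampling strategies), the cohort's established systems are used to keep participation high (Table 2, Phase I), and people who have not fasted are asked to return (OGTT and biological sample collection). These may reduce non-response. They do not adjust for what remains.
- **That the national rural share measures the error.** Study setting says that more than "70% of the population still lives in rural areas", but as background. The formal primary objective does not claim national prevalence, and reweighting two areas of one region to that share would not make them represent the country.
- **That the response rate is really about 60%.** The Abstract's ceiling of 11 700 over 18 864 adults is 62%. That is an enrolment cap over a frame that includes ineligible people. Adults not screened because a target was reached are not non-responders, and leaving them out causes no bias if screening is random, as Sample size determination says.

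**Conclusion.** The point holds at moderate weight and should be corrected. Followed as written, the primary estimate moves with differential attendance and with the balance of the two sites, and the allowance described in the Discussion does nothing to prevent this. At the planned 80% response, an assumed gap of 1.5 to 2.5 points between responders and non-responders gives a bias of 0.3 to 0.5 points against a planned margin of 0.5. Only the upper end of that range reaches the full margin.

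The sizes rest on assumed prevalences. They show that the estimate is sensitive; they do not show that it will be wrong by that amount. The calculation of 7300 and 10 950 stands. The descriptions of the target population disagree, since a rural population and the whole country are both named while the frame is one rural and one periurban area.

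**What to change.** - **Estimator.** Report prevalence of diabetes and pre-diabetes by site, weighted to the GPC census and the Lukaya enumeration, by age and sex where those counts are available. Give a pooled figure only with its site weights stated, about 47:53 from 8864 and about 10 000 adults.
- **Target population.** Name the two study areas as the one target, replacing the rural Ugandan population in the Abstract and the national wording in the Introduction.
- **Discussion.** Say that the allowance for unresponsiveness protects precision. Do not present it as reducing bias.

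The cost is analysis and wording: no more participants, slightly wider intervals and two headline numbers in place of one. The site margins of about ±0.73 and ±0.69 points remain within the plan's acceptable range.

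Two limits should be stated with the result. Weighting corrects only for differences captured by site, age and sex, so selection within those groups remains. The Lukaya count is approximate, and the article does not show its age and sex breakdown.

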### Study status

This manuscript describes version 1.2 of our protocol. Enrolment in the study began in
January 2022. The anticipated end to patient enrolment is November 2023.
